### Follow-up schedule and outcome assessment

Patients will be visited twice daily during the first seven days after surgery for assessment of delirium and monitoring of non-delirium complications. They will then be followed up weekly until 30 days after surgery for monitoring of non-delirium complications and assessment of outcome. Detailed perioperative data including duration of anesthesia, doses of sedatives, anesthetics and analgesics used during anesthesia, type and duration of surgery, intraoperative fluid balance and transfusion of blood products, use of drugs with anticholinergic properties as well as postoperative analgesic consumption will be collected.

For patients who develop delirium, management will be administered according to routine practice, i.e., nonpharmacologic treatment will be applied first, pharmacologic treatment will be reserved only for those with severe agitation. Meanwhile, potential causes will be searched and corrected [55, 56].

#### Primary outcome

The primary outcome is the 7-day incidence of postoperative delirium. Patients will be assessed for delirium with the CAM-ICU twice daily (from 8 to 10 a.m. and from 6 to 8 p.m.) during the first seven days after surgery. Study personnel who assess delirium do not participate in intraoperative anesthesia and postoperative management of patients.

#### Secondary outcomes

Secondary outcomes include the duration of postoperative delirium, the intensity of pain during the first three days after surgery, the occurrence of non-delirium complications within 30 days after surgery, the length of stay in hospital after surgery, and the 30-day all-cause mortality.

The intensity of postoperative pain both at rest and with coughing will be evaluated twice daily at the same time of delirium assessment (i.e., from 8 to 10 a.m. and from 6 to 8 p.m.) with the numeric rating scale (NRS, a 11-point scale where 0 indicates no pain and 10 indicates the worst pain). For patients who are deeply sedated or unarousable (−4 or −5 on the RASS), pain evaluation will be stopped temporarily and repeated later. Analgesic consumption will be recorded daily during the first three days after surgery. Non-delirium complications are defined as medical conditions other than delirium that required therapeutic intervention.

### Adverse events

An adverse event indicates any unpredictable, unfavorable medical event that is associated with any medical intervention and occurs during the study period. It can be related to the study intervention or otherwise. All adverse events will be monitored carefully, managed promptly according to routine practice, and followed up until they are properly resolved, stabilized or recovered to normal. The information including the type, date(s) of onset and resolution (if applicable), severity of influence, relationship with grouping, treatment and outcome (sequelae) will be recorded in the Case Report Forms. They will be reported to the IRB in the final report.

A severe adverse event indicates any unpredictable medical events that lead to death, threat of life, prolonged length of hospital stay, persistent disability or dysfunction, or other severe event. All severe adverse events will be monitored, managed, followed up and recorded as above, and will be reported to the IRB within 24 hours after their occurrence.

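### Both safety definitions cover only unpredictable events, so a foreseeable harm, even a life-threatening one, falls outside adverse-event recording and the 24-hour IRB report

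*Protocol article*

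**What the plan says.** The Adverse events section gives two definitions. The general one reads "An adverse event indicates any unpredictable, unfavorable medical event that is associated with any medical intervention and occurs during the study period", followed by "It can be related to the study intervention or otherwise". The severe category repeats the qualifier: "A severe adverse event indicates any unpredictable medical events that lead to death, threat of life", and goes on to prolonged stay, lasting disability or dysfunction, and a catch-all for other severe events.

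The duties in that section attach to these definitions. Adverse events are followed until they resolve or stabilise. They are entered in the case report form with type, dates, severity, relation to the allocated group, treatment and outcome, and they go to the IRB in the final report. Severe adverse events get the same handling and, in addition, "will be reported to the IRB within 24 hours after their occurrence".

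Elsewhere, the Secondary outcomes section has a separate definition: "Non-delirium complications are defined as medical conditions other than delirium that required therapeutic intervention". The Follow-up section sets the schedule for monitoring these complications.

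**The concern.** The restriction is part of both definitions, so it is hard to treat as one slip of the pen. The trial compares two established techniques, and the harms of established techniques are largely of known kinds. A definition that admits only unpredictable events sits badly with that. A site that follows the text could see a serious event of a well-known kind, judge that it is not a severe adverse event, and send no expedited report.

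At stake is mainly patient safety oversight: whether the IRB hears promptly of serious events of a foreseeable kind. A second, smaller matter is whether some harms are written down anywhere with their severity and their relation to the allocated group.

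**Working it through.** No arithmetic applies. The check sets the relevant sections of the protocol article side by side.

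1. **Does another sentence lift the restriction?** The one candidate is "It can be related to the study intervention or otherwise". It concerns relatedness, not expectedness. An event can be related and foreseeable, so the restriction stays.

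2. **Does the protocol itself foresee harms?** Yes. Participants lists contraindications to epidural block, among them coagulation disorder and infection near the puncture site, which implies that bleeding and infection are foreseen. The EGA section checks the aspirate for blood and cerebrospinal fluid before the test dose. The opening paragraph on anesthesia provides for treatment of bradycardia. Both analgesia sections allow lower doses and a dose limit for frail patients. The excluded class is therefore not empty.

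3. **What is captured by another route?** Non-delirium complications depend on treatment, not on predictability. The schedule is "Patients will be visited twice daily during the first seven days after surgery for assessment of delirium and monitoring of non-delirium complications" and then "They will then be followed up weekly until 30 days after surgery for monitoring of non-delirium complications and assessment of outcome". The secondary outcomes also include "the length of stay in hospital after surgery, and the 30-day all-cause mortality", and delirium is the primary outcome.

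4. **Which data carry the comparison between arms?** Data analysis names the incidences of non-delirium complications and 30-day mortality for chi-squared or Fisher tests, and time to complications for Kaplan-Meier and log-rank methods. It names no adverse-event count.

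5. **What is left uncovered?**

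| Foreseeable harm | Recorded elsewhere? | 24-hour IRB report? |
|---|---|---|
| After surgery, treated, to day 30 | Yes, as a complication | No, even if severe |
| Death within 30 days | Yes, as mortality | No |
| During catheter placement or surgery | No stated route | No, even if severe |
| After surgery, no treatment needed | No stated route | No, even if severe |
| Event-level severity, relation to group, follow-up to resolution | Not stated for complications | Not applicable |

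The third row follows from timing. Randomization takes place just before anesthesia and the EGA group has its catheter placed first, whereas the complication outcome is framed as within 30 days after surgery. The perioperative data listed under Follow-up are durations, doses, fluids, transfusion and drug use; no intraoperative event is named. For that window the Adverse events section is the only stated rule for recording harm, and catheter placement occurs in one arm only.

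**The case against.** The strongest reply is that the word is loose drafting for untoward, or means not predictable in the individual patient. The case report form asks for the relation of each event to the allocated group, which would have little purpose if known technique-related harms were excluded. This may well be what the sponsor intends. If so, the amendment changes nothing intended and only makes the text say it. It does not make the written rule correct.

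A second reply is that a journal article condenses the full protocol, where detailed safety instructions would normally sit. That disposes of any complaint that expectedness rules are absent. It does not reach a definition that the article states, and states twice.

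Several stronger readings are tempting, and the document does not support them:

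- A reader might infer that foreseeable harms go unrecorded altogether. The complication and mortality outcomes show otherwise for treated postoperative conditions and for deaths.
- A reader might infer a biased comparison of harms, with open-label staff filtering events by expectedness. No such classification step is described, and the analysed outcomes do not pass through the adverse-event definition.
- A reader might see a contradiction between association with any medical intervention and the sentence on relatedness. The two can coexist, because the association may be with surgery or other care.
- The catch-all for other severe events gives no criterion, but it widens the severe category and so works against under-reporting.

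**Conclusion.** The point holds in a limited form. On the literal text, a foreseeable harm is outside adverse-event recording and, if severe, outside the 24-hour IRB report. The reporting gap has no substitute in the document. The recording gap is confined to foreseeable harms during catheter placement and surgery, harms that needed no treatment, and the event-level adverse-event items.

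Its size cannot be estimated: the document gives neither a list of expected harms nor rates for them, so a statement about what share of harms is affected would be unsupported. The planned between-arm analyses of complications and mortality are not undermined, and neither the primary analysis nor the sample size is touched. The conclusion assumes that sites apply the definitions as printed and that the full protocol, which is not shown, does not word them differently.

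**What to change.** - Delete the word unpredictable from both definitions, so that events count whether or not they were expected.
- Record expectedness as its own item in the case report form, next to the existing item on relation to the allocated group.
- State how non-delirium complications and adverse events overlap, and that a complication meeting the severe outcome criteria is also reported to the IRB within 24 hours.

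The cost is a wording amendment with IRB approval, one added form item, brief retraining of study personnel, and somewhat more events to record and report.

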### Sample size estimation

In a recent cohort study of our own, the incidence of postoperative delirium in elderly patients after major abdominal surgery (performed under general anesthesia followed by intravenous analgesia) was 13.1 %. In our previous study, the incidence of delirium was reduced by roughly 1/3rd when the intervention (haloperidol prophylaxis) was administered in elderly patients after noncardiac surgery [57]. Assuming that the GA Group (general anesthesia plus postoperative intravenous analgesia) in the present study will have a similar delirium incidence as in our previous study, a total of 1664 subjects (832 subjects in each group) are required to detect a 30 % reduction in the incidence of postoperative delirium at a 90 % power with a two-sided significance level of 0.05. Considering a dropout rate of about 7.5 %, we plan to enroll 1800 patients during a 3-year period.

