#### Combined Epidural-General Anesthesia plus Postoperative Epidural Analgesia (EGA Group)

For patients assigned to receive combined epidural-general anesthesia plus postoperative epidural analgesia (EGA Group), epidural catheterization will be performed first. The intervertebral space for epidural puncture will be selected by the attending anesthesiologists according to the site of planned incision. An epidural catheter will be inserted using a standard technique. After negative aspiration for blood and cerebrospinal fluid, a test dose of 3–4 mL of 2 % lidocaine will be administered to confirm the position of the catheter.

General anesthesia will also be induced with midazolam (0.02-0.03 mg/kg), propofol, sufentanil and rocuronium. Anesthesia will be maintained with intravenous (propofol), inhalational (sevoflurane with or without nitrous oxide), or combined intravenous-inhalational anesthetics, together with 0.375 %–0.5 % ropivacaine administered bolusly and/or continuously through the epidural catheter. Additional opioids (remifentanil, sufentanil, fentanyl, or morphine) and muscle relaxant (rocuronium, atracurium, or cisatracurium) will be administered when deemed necessary.

Patient-controlled epidural analgesia will be provided after surgery. This is established with 0.12 % ropivacaine and 0.5 μg/mL sufentanil in 250 mL normal saline, programmed to deliver a 2-mL bolus with a lockout interval of 20 minutes and a background infusion of 4 mL/hr. For patients with low body weight or poor general condition, doses can be decreased and upper dose limit can be set for the patient-controlled pump.

All anesthesiologists participating in the study will be experienced in epidural block techniques. But even in experienced hands, we can anticipate a failure rate of about 5 %. Patients with unsuccessful epidural blocks will receive general anesthesia and postoperative intravenous analgesia as that for the GA Group. However, data of these patients will be included in the EGA Group in the final intention-to-treat analysis (Fig. 1).

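### On the only control incidence given (13.1%), 832 patients per group have about 72% power for a 30% reduction in delirium, not the stated 90%

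*Protocol article*

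**What the plan says.** All of the design inputs stand in the Sample size estimation section of the protocol article.

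- **Control incidence.** A cohort study by the same group, in elderly patients after major abdominal surgery, supplies the rate: "performed under general anesthesia followed by intravenous analgesia) was 13.1" percent.
- **Which rate is assumed.** The GA group "in the present study will have a similar delirium incidence as in our previous study". The section has by then mentioned two studies: the cohort, and a trial of haloperidol prophylaxis.
- **Effect seen elsewhere.** In the haloperidol trial, "the incidence of delirium was reduced by roughly 1/3rd".
- **Target effect, power and level.** The aim is "to detect a 30 % reduction in the incidence of postoperative delirium", with 90% power and a two-sided level of 0.05.
- **Result.** The section concludes that "a total of 1664 subjects (832 subjects in each group) are required to detect" this effect, and raises the total to 1,800 for about 7.5% dropout.

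The Study design section gives equal allocation, 900 per group. The Data analysis section names a Cochran-Mantel-Haenszel test stratified by center and type of surgery, analysed by intention to treat.

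**The concern.** The section prints a complete set of inputs together with a sample size, so the one can be checked against the other without any further document. A fall from 13.1% to 9.17% is a difference of 3.93 percentage points, and 832 per group looks too few to detect it with 90% power.

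This calculation is the whole justification for the size of the trial, and the Discussion lists the large sample as a strength. If the power is overstated, the ethics board and readers have been given the wrong type II error for the primary outcome. A non-significant result would then be taken as stronger evidence against a 30% reduction than the design can supply.

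**Working it through.** **Inputs.** From Sample size estimation: p1 = 0.131; a 30% relative reduction gives p2 = 0.7 × 0.131 = 0.0917; difference d = 0.0393; two-sided 0.05 (z = 1.960); 90% power (z = 1.2816). From Study design: 1:1 allocation.

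**Step 1: the plan's own figures.** The dropout step reproduces: 1,664 / (1 − 0.075) = 1,799, or about 1,800. The 832 per group does not, as the next step shows.

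**Step 2: size needed for 90% power.** With the usual pooled-variance formula for two proportions,

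n = [1.960 × √(2p̄(1 − p̄)) + 1.2816 × √(p1(1 − p1) + p2(1 − p2))]² / d²

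- p̄ = (0.131 + 0.0917)/2 = 0.11135
- √(2p̄(1 − p̄)) = 0.4449; times 1.960 = 0.8719
- √(p1(1 − p1) + p2(1 − p2)) = 0.4440; times 1.2816 = 0.5690
- n = (0.8719 + 0.5690)² / 0.0393² = 1,344.3, so **1,345 per group**, or 2,690 evaluable patients

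Unpooled variance gives 1,342, the arcsine method 1,337, and the continuity correction 1,395.

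**Step 3: power at the planned size.** Power = Φ{[d√n − 0.8719] / 0.4440}.

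- n = 832: (1.1336 − 0.8719)/0.4440 = 0.589, so power = **72.2%**. A simulated unstratified chi-squared test gives 72.3%.
- n = 900: (1.1790 − 0.8719)/0.4440 = 0.692, so power = **75.5%**.

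The type II error at 832 is 27.8%, which is 2.8 times the stated 10%.

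**Step 4: other readings of the inputs.**

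| Reading | Per group for 90% power | Power at 832 |
|---|---|---|
| As stated | 1,345 | 72.2% |
| One-sided 0.05 | 1,096 | 81.7% |
| Exact one-third reduction (to 8.73%), two-sided | 1,070 | 81.6% |
| 30% reduction in odds (to 9.55%) | 1,668 | not computed |

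None gives 832 at 90% power.

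**Step 5: what 832 per group can detect from 13.1%.** Solving the power formula for the effect gives 90% power at a reduction of about 37% (to about 8.2%), and 80% power at about 33%.

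**Step 6: the control rate that would make the statement true.** Holding the 30% reduction, 90% power and n = 832, the GA rate would have to be about 19.8%. The article gives no such rate. The incidences in the Background (36.8%, 44.5% and 51%) would need only 369, 276 and 219 per group, so none of them produces 832 either.

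**The case against.** **The control rate is not pinned down.** The assumption refers to a previous study, and the sentence just before it uses that label for the haloperidol trial, whose control rate is not given. If that rate were about 19.8%, the stated figures would agree. This stands as a caveat. It does not rescue the paragraph: 13.1% is the only incidence in the section, it is reported for the same anesthesia and analgesia as the GA arm, and nothing in the article supports 19.8%. If another rate was used, the section still has to state it.

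**The origin of 832.** A reader might infer that both the power and the effect were misreported, because 13.1% versus 8.7% at 80% power with continuity correction gives 831.1, rounded up to 832. The documents do not support that as a finding. The match depends on rounding the EGA rate to 8.7%; an exact one-third reduction gives 845 by the same formula. It is one possible origin for the sponsor to check.

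**Failed epidurals.** The EGA Group section says that "even in experienced hands, we can anticipate a failure rate of about 5" percent, with those patients treated as GA but analysed as EGA. A reader might infer that the sample size makes no allowance for this. That is not shown. The 30% can be read as the intention-to-treat effect, and a one-third effect diluted by 5% is 0.95 × 33.3% = 31.7%, still above 30%. Only if the 30% is the effect in successful blocks, and failed blocks gain nothing, does the EGA rate become 0.95 × 9.17% + 0.05 × 13.1% = 9.37%. Power at 832 is then about 67%. That is a sensitivity figure, not an error in the plan.

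**The consequence is limited.** Data analysis commits to a 95% confidence interval for the difference, which will show what a null result excludes whatever the planned power. The 28% miss rate also assumes the full 7.5% loss; with all 1,800 analysed it is about 24%. Both points are fair. They soften the harm but do not make the 90% correct.

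**Conclusion.** The point holds. On the only control incidence the section gives, the claim of a 30% "reduction in the incidence of postoperative delirium at a 90 % power with a two-sided significance level of 0.05" does not follow from 832 per group. The power is about 72% (about 76% with 900 per group), a shortfall of about 18 points at 832. Reaching 90% would take about 1,345 per group, or about 2,909 enrolled at 7.5% dropout (2,690/0.925).

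This rests on a GA incidence of 13.1%, a relative reduction of 30%, equal groups, and an unstratified two-proportion test as an approximation to the stratified one. Stratification by center and type of surgery could not plausibly close a gap of this size.

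The conclusion depends on the baseline: 90% would be right at about 19.8%, a rate the article does not report. It depends neither on any account of where 832 came from nor on the epidural failures.

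**What to change.** Keep the enrolment of 1,800. In Sample size estimation:

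1. Name the study that supplies the control rate, and give the rate used.
2. Restate the power by a single method. If 13.1% is confirmed, suitable wording would be: *Assuming a delirium incidence of 13.1% in the GA group, 832 evaluable patients per group give, at a two-sided 0.05 level and without continuity correction, about 72% power for a 30% reduction, about 82% for a one-third reduction, and 90% for a reduction of about 37%.*
3. If a different control rate was used, state it and its source, and recompute from it.
4. Check the original calculation, including whether 13.1% versus 8.7% at 80% power with continuity correction was the actual basis.
5. Optionally, add the 67% sensitivity figure with its two assumptions (the 30% applies to successful blocks; failed blocks gain no benefit).

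The cost is wording and a less favourable stated power, with no extra patients. The Trial status section says recruitment is under way, so the correction is best made before results are known; made afterwards, it would look post hoc.

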### Data analysis

All statistical analyses will be performed with SAS statistical package, version 9.3 (SAS Institute, Cary, NC, USA) by statisticians at Peking University Clinical Research Institute. Analyses will be done on an intention-to-treat basis, that all subjects will be analyzed in the group which they were assigned to.

Primary outcome (the 7-day incidence of postoperative delirium) will be analyzed using Cochran-Mantel-Haensel Chi-squared tests, stratified by medical center and type of surgery (thoracic or abdominal surgery). The 95 % confidence interval of the incidence of each group and the difference between the two groups will be calculated. Logistic regression will be used for further analysis if an adequate number of events are observed or any impact or relative factor is expected according to the results of single-factor analysis. For the secondary outcomes, continuous variables (the dose of medications, the NRS pain scores after surgery) will be analyzed using an unpaired T-test, Mann–Whitney U test or repeated-measure analysis of variance; categorical variables (the incidences of non-delirium complications, the daily prevalence of delirium, and the 30-day mortality rate) will be analyzed using the Chi-squared test, continuity correction Chi-squared test or Fisher exact test; time-to-event results (time to onset of delirium or non-delirium complications, duration of hospitalization after surgery) will be analyzed using the Kaplan-Meier estimator, and the differences between groups will be tested by the log-rank test. Also the Cox proportional hazards model will be used to estimate the overall survival HR and 95 % confidence interval.

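### Pain scores repeated over three days are given a choice of three methods; one stratum-adjusted mixed model per condition would use the data better and close off the weaker options

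*Protocol article*

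**What the plan says.** The Secondary outcomes section of the protocol article lists "the intensity of pain during the first three days after surgery" and sets the schedule: "The intensity of postoperative pain both at rest and with coughing will be evaluated twice daily at the same time of delirium assessment". The instrument is the NRS, "a 11-point scale where 0 indicates no pain and 10 indicates the worst pain". For patients at RASS −4 or −5, "pain evaluation will be stopped temporarily and repeated later".

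The Data analysis section groups pain with drug doses: "continuous variables (the dose of medications, the NRS pain scores after surgery) will be analyzed using an unpaired T-test", and the list ends with "U test or repeated-measure analysis of variance". It does not say which method applies to pain, which time point or patient-level summary would enter a two-sample test, or which form of repeated-measures analysis is meant. It also states: "Analyses will be done on an intention-to-treat basis, that all subjects will be analyzed in the group which they were assigned to".

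The Randomization section stratifies by centre and by thoracic or abdominal surgery. The Data analysis section carries both factors into the primary test, but not into the methods named for pain.

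**The concern.** The three methods do not answer the same question. A t-test or Mann–Whitney test takes one value per patient, so with repeated scores it needs a named time point or summary, and none is named. Used separately at each assessment, these tests produce several correlated comparisons without adjustment. Repeated-measures ANOVA does use the series, but its classical form keeps only patients with every score. As named, none of the three takes account of centre or type of surgery, and thoracic and abdominal incisions may plausibly differ in pain.

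What is at stake is a secondary outcome that carries part of the rationale. The Background section names intense postoperative pain as a precipitating factor for delirium and cites better pain relief with epidural analgesia. Pain is self-reported in an open-label trial, so freedom in choosing the analysis adds to an exposure to bias that already exists.

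**Working it through.** The article gives no sample size, power or effect for pain, so it has no figure of its own to reproduce. The correlations and missed-score rates below are assumptions and are shown as ranges.

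**Number of scores.** Two per day × 3 days = about 6 assessments per condition. Two conditions (rest, coughing) give about 12 scores per patient.

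**Single-time tests at two-sided 0.05, no adjustment, no true difference at any time.**
- Independent tests: 1 − 0.95^6 = 26.5%; 1 − 0.95^12 = 46.0%.
- Equicorrelated normal test statistics (400,000 simulated draws), chance of at least one false positive:

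| Assumed correlation | 6 tests | 12 tests |
|---|---|---|
| 0.3 | 24% | 40% |
| 0.5 | 21% | 32% |
| 0.7 | 16% | 23% |
| 0.9 | 11% | 13% |

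**One summary instead of six tests.** A null simulation used NRS-like scores: 200 patients per arm, six assessments, correlation 0.5. At least one of the six t-tests was significant in 20.9% of runs. A single t-test on the patient mean was significant in 4.9%. Taking the smallest p-value across t-tests, Mann–Whitney tests and the mean-score test gave 23.5%. Most of the inflation therefore comes from testing at repeated times, and little from choosing between tests.

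**Complete-case ANOVA over six assessments.** If a proportion m of scores is missed, independently at each assessment, the share of patients dropped is 1 − (1 − m)^6.
- m = 2%: 1 − 0.98^6 = 11.4%, about 103 of 900 per arm.
- m = 5%: 1 − 0.95^6 = 26.5%, about 238 of 900 per arm.
- If the same patients miss every score, the loss falls to m itself: 2–5%, or 18–45 of 900 per arm.

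**Precision compared with a single time point.** With correlation ρ, the mean of six scores has variance (1 + 5ρ)/6 relative to one score.
- ρ = 0.5: 3.5/6 = 0.58, equivalent to 1/0.58 = 1.7 times as many patients.
- ρ = 0.7: 4.5/6 = 0.75, equivalent to 1/0.75 = 1.3 times as many patients.

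This gain is over a single-time analysis only. Repeated-measures ANOVA, already on the list, also averages over the six scores.

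**The case against.** A reader might infer that the plan must lead either to a dozen unadjusted tests or to the loss of every patient with one gap. The text does not support that. It does not say that tests are run at each time, and it does not say that incomplete patients are dropped. A t-test on a patient mean or area under the curve is one valid test, and a repeated-measures model fitted by likelihood in SAS keeps incomplete patients. The list can also be read as matching method to data: two-sample tests for doses, repeated-measures ANOVA for pain. All of this stands, and it limits the point to what the wording permits.

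It is also fair that deferred scoring is meant to recover scores, that it applies only to very deep sedation, and that the Discussion expects most patients not to be in the ICU and intubated. The documents give no missed-score rate and no evidence that gaps differ by arm. The independence assumption overstates the loss if gaps cluster in sicker patients. The error rates assume no pain difference at any time, whereas the Background cites studies that found one. Omitting the strata mainly costs precision and does not inflate false positives.

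Finally, this is a condensed article, and covariance structure or missing-data rules may be in an analysis plan that is not shown. Their absence is not the point. The article does state methods for pain, and a better one can be named at almost no cost: it uses the strata, keeps incomplete patients and yields one result per condition.

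**Conclusion.** The point holds in a limited form. For a repeated outcome the article offers three non-equivalent methods. They permit unadjusted single-time testing (illustratively 16–21% familywise error for six tests and 23–32% for 12, at correlations of 0.7–0.5) or a complete-case ANOVA (illustratively 11–26% of patients lost if 2–5% of scores are missed independently, and as little as 2–5% if gaps fall in the same patients). They do not require either. None of the methods as named uses the two randomization factors, which the primary analysis does use.

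The percentages show scale and are not predictions, because the correlations, missed-score rates and independence are all assumed. The issue is confined to one secondary outcome. It would be wrong to infer that the delirium result is at risk: the stratified primary test does not depend on how pain is analysed.

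**What to change.** For NRS pain, replace the list with one linear mixed model for rest and one for coughing, each using all available scores. Include group, assessment time, group-by-time, centre and type of surgery, and allow for correlation within patients. Report the group difference averaged over the six assessments, with its 95% CI, as the single result for each condition. Present single-time differences as descriptive. Keep the t-test or Mann–Whitney test for one-off quantities such as drug doses.

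The cost is a few sentences in the analysis plan and a standard procedure in the SAS package already named. No new data and no change in conduct are needed. The Trial status section says recruitment is still under way, so the method can be fixed before results are known.

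There are two downsides. The result is a mean difference on a bounded 0–10 scale, which is acceptable at about 900 per arm. The model also assumes that scores are missing at random, so it reduces bias from sedation-related gaps but may not remove it.
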